### Trial design {8}

The STAR (Study of Trauma And Recovery) trial is a rater-blind, parallel arm RCT comparing an integrated therapy to address post-traumatic stress and psychosis symptoms (TF-CBTp) in addition to TAU, to TAU alone, in individuals with co-morbid PTSD and psychosis across five sites. Randomisation will be in the ratio 1:1 to the two groups and will be stratified by centre. It will be a pragmatic clinical and cost-effectiveness superiority trial.

An internal pilot study will ensure the integrity of trial recruitment; protocol safety and adherence; and outcome data [60]. The internal pilot will last 16 m following the start of recruitment and will include three checks for each of these categories, at 6, 12, and 16 m post recruitment start.

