### Intervention description {11a}

#### Trauma-Focused Cognitive Behaviour Therapy for psychosis (TF-CBTp)

TF-CBTp is a manualised therapy integrating standard psychological therapy for PTSD and for psychosis [3, 8, 20, 25–27, 31]. It will be delivered over a period of 9 m. Approximately 26 weekly or bi-weekly individual 60–90-min sessions will be offered in the first 6 m. Bi-weekly rather than weekly sessions have a potential to be beneficial during the trauma reprocessing phase of the therapy [70, 71] but it will be left to participant choice. A further three sessions will be offered on a monthly basis during the next 3 m, to consolidate therapeutic gains. They will be done jointly with the care coordinator, if possible, to assist with generalisability of therapy effects. Therapists will liaise with clinical teams throughout the delivery of therapy to discuss progress, with the participant’s consent, and to share any potential risk to self or others.

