#### Data confidentiality

Research data will be confidential unless a participant discloses information that indicates that they or another person are at risk of harm. If harm is disclosed, the research worker or trial therapist would be required to share this information with the participant’s care team and documented in the NHS trust’s electronic patient record system.

All research data will be pseudonymised. A hard copy of a record sheet linking Participant Identifiable Data (PID) (participant identity, contact details, trial identification number) for all participants will be kept separate from the research data at each site. The participant record sheet, and details necessary for communication with clinical teams, will be placed securely in locked filling cabinets separate from research datasheets. During the COVID-19 pandemic, staff may have to work remotely outside of Trust premises; an electronic version of the record sheet linking PID will be created and saved on secure Trust drives accessible online.

All data will be kept secure at all times and maintained in accordance with General Data Protection Regulation (GDPR, 2018) requirements and archived according to clinical trial Good Clinical Practice regulations. Participant consent forms will be retained, kept confidential, and stored securely. All identifiable data will be destroyed following a period of 10 years (as determined by relevant information governance policies) after the completion of the trial.

No participant identifiable information is recorded on the research assessment records and the computerised database is held centrally and managed by the KCTU. Data from the assessments are entered into this central record by research workers using a secure network connection.

Therapy files will be kept in a secure office and are not accessible to the staff collecting the research outcome data.

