### Adverse event reporting and harms {22}

Best practice, professional guideline, and local NHS policies for monitoring mental state and risk will be followed throughout the participants’ involvement in the trial and will be facilitated by close liaison with clinical teams. The safety of the intervention will be monitored closely during therapy sessions and through regular contact with the participant’s clinical team or GP.

The occurrence of adverse events (AEs) will be monitored actively and systematically and recorded by research workers and therapists, following guidance from the CONSORT-SPI [74] with the extension for non-pharmacologic treatment, and the extension for reporting of harms. Reasons for withdrawal from the study will also be recorded. Medical Research Council Guidelines for Good Clinical Practice in Clinical Trials will also be followed to ensure good governance of the trial for integrity and participants’ safety and well-being.

To ensure active surveillance of harms, at each assessment point, research workers will actively check for the occurrence of specific AEs using a structured checklist completed with the participant. Clinical notes will additionally be checked by unblinded members of the research team for any further undisclosed record of AEs. This extra procedure is to ensure completeness of records and to address the possibility of an increased likelihood of disclosure of AEs in the TF-CBTp condition, as a result of greater frequency of contact and the therapeutic relationship.

Good Clinical Practice guidance for non-CTIMPs (Clinical Trial of an Investigational Medicinal Product) studies will be followed to make decisions regarding seriousness (i.e. AEs vs SAEs), relatedness to the trial (i.e. Related Events (REs) and serious related events (SREs), and unexpected serious related events (USREs).

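### Adverse event counts pooled over all sources can lean towards apparent excess harm in TF-CBTp, and the clinical-notes check only partly corrects this

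*Protocol article*

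**What the plan says.** The section on adverse event reporting and harms {22} has AEs "monitored actively and systematically and recorded by research workers and therapists". It adds: "The safety of the intervention will be monitored closely during therapy sessions and through regular contact with the participant’s clinical team or GP".

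The same section sets up a source common to both arms. At each assessment point, "research workers will actively check for the occurrence of specific AEs using a structured checklist completed with the participant". The participant timeline and the assessment procedure say that follow-up assessments are done by research workers blind to group.

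Unblinded staff also search the clinical notes. The stated reasons are completeness and "to address the possibility of an increased likelihood of disclosure of AEs in the TF-CBTp condition".

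Two other sections show how therapy disclosures can reach those notes:

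- The description of TF-CBTp says "Therapists will liaise with clinical teams throughout the delivery of therapy to discuss progress", with the participant's consent, and to share risk.
- Under data confidentiality, when risk of harm is disclosed, a research worker or trial therapist "would be required to share this information with the" participant's care team, and the disclosure goes into the trust's electronic record.

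The items the protocol lists for each AE are cause, severity, seriousness, relatedness and unexpectedness. The source that identified the event is not among them. The section on auditing {23} says that closed DMEC reports show data split by treatment group.

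**The concern.** Trial therapists offer about 26 sessions in the first 6 months and 3 more by 9 months. The only therapist contact described for TAU is being told the allocation. By 9 months the scheduled common source is two post-randomisation checklists, at 4 and 9 months. An event mentioned only in therapy is therefore counted in TF-CBTp, while its equivalent in TAU may never be counted.

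The protocol's own remedy is not independent of the problem, because therapists contribute to the notes being searched. Searching them raises capture in both arms, but it does not take out events known only through therapy.

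Safety is described as an important subsidiary goal. The DMEC reviews SAE incidence, may investigate rates that seem too high, and advises on continuation. Any AE rated severe becomes an SAE, so unequal capture is not confined to minor events. The error can run both ways: a tilt from ascertainment may be read as harm, or a real excess may be dismissed as greater disclosure. If the source was not recorded, the data may not be able to separate the two.

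**Working it through.** **No plan figure to reproduce.** The protocol gives no AE rate, capture probability or between-arm harm figure. What follows is an illustration under assumed values.

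**Model.** Equal true AE risk in both arms and independent channels:

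- c = share of AEs caught by the checklist, same in both arms (assumed 0.5 to 0.9)
- b = share caught by the notes from entries not originating with the therapist, same in both arms (assumed 0.3 to 1.0)
- s = share caught by the therapist, TF-CBTp only (assumed 0.2 to 0.5)

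TAU captured = 1 − (1 − c)(1 − b)

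TF-CBTp captured = 1 − (1 − c)(1 − b)(1 − s)

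| c | b | s | TAU | TF-CBTp | Ratio |
|---|---|---|---|---|---|
| 0.5 | 0.3 | 0.5 | 0.650 | 0.825 | 1.27 |
| 0.5 | 0.6 | 0.5 | 0.800 | 0.900 | 1.13 |
| 0.5 | 0.9 | 0.5 | 0.950 | 0.975 | 1.03 |
| 0.7 | 0.6 | 0.2 | 0.880 | 0.904 | 1.03 |
| 0.9 | 0.9 | 0.5 | 0.990 | 0.995 | 1.005 |
| 0.5 | 1.0 | 0.5 | 1.000 | 1.000 | 1.00 |

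First row: 1 − 0.5 × 0.7 = 0.65, and 1 − 0.5 × 0.7 × 0.5 = 0.825.

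**What the notes check achieves.** Without it, the ratio at c = 0.5, s = 0.5 is (1 − 0.5 × 0.5)/0.5 = 1.50, and at c = 0.7, s = 0.5 it is (1 − 0.3 × 0.5)/0.7 = 1.21. With b = 0.3 these fall to 1.27 and 0.895/0.79 = 1.13. The check helps, but the ratio reaches 1.00 only when the notes are complete.

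**Why feeding the notes matters.** Suppose therapists' direct reports were dropped but half of what they hear still reached the notes. At c = 0.5, b = 0.3, s = 0.5, TF-CBTp captures 1 − 0.5 × 0.7 × (1 − 0.25) = 0.7375. The ratio is 0.7375/0.65 = 1.13, so part of the bias survives through the notes.

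**Scale against chance.** With 150 per arm and an assumed true risk of 40%, the first row gives observed risks of 0.4 × 0.65 = 26% and 0.4 × 0.825 = 33%. A nominal two-sided 5% test would then show a spurious TF-CBTp excess about 26% of the time, against 2.5% when the notes are complete. The protocol describes no such test; this only gives a sense of scale.

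**Comparison on common sources.** If only the checklist and notes entries not originating with the therapist count, both arms capture 1 − (1 − c)(1 − b). The ratio is 1.00 for every c and b, provided c and b really are equal across arms.

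**Follow-up period.** The internal pilot "will include three checks for each of these categories, at 6, 12, and 16 m post recruitment start", with protocol safety among the categories. Under even accrual, 300/22 = 13.6 join per month. At 6 months, 6 × 13.6 = 81.8 are randomised, about 41 per arm. Of these, 2 × 13.6 = 27.3, about 14 per arm, have reached a 4-month checklist. If the 1-month window is used early, it is 3 × 13.6 = 40.9, about 20 per arm. Therapists may already be recording for most of the 41 in TF-CBTp. The notes check may cover some of this interval in both arms; the protocol does not say when it is done.

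**The case against.** The case on the other side is substantial:

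- The structured checklist is applied in the same way in both arms, by blinded research workers at follow-up. The service-use schedule also covers both arms.
- The notes are not simply the therapists' record. Care coordinators and psychiatric appointments generate entries in both arms, and research workers must also pass on risk disclosures. The confidentiality rule concerns risk of harm, not every AE, and therapist liaison needs consent.
- AEs are largely defined by a need for professional input, so many will be in the notes whoever heard first. Most SAE categories, such as death or admission, depend little on disclosure to a therapist.
- Each AE already has a cause code that includes therapy, so therapy-specific distress can be separated. Distress about group allocation could fall on TAU.
- Therapy ends at 9 months, so the extra channel closes for the last 15.
- No formal between-arm AE analysis is described here. The AE form, the analysis plan and the DMEC report template are not shown.

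All of this limits the size, and it could bring the bias close to zero. It does not remove the mechanism, which the protocol itself names and answers with a remedy that only partly works. How each event was identified is a matter of data collection: if it is not captured at the time, an analysis plan may be unable to recover it.

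**Conclusion.** The point holds as a possible bias of unknown size. All-source AE and SAE counts can tilt towards apparent excess harm in TF-CBTp, and the notes check reduces the tilt without removing it unless checklist or notes capture is nearly complete. With no true difference and the assumed capture rates, the ratio runs from 1.00 to about 1.3. This rests on independent channels and on assumed values of c, b and s.

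A reader might infer that the trial will show excess harm even if there is none, or that a ratio of 1.5 is to be expected. The documents do not support either. No capture rates are given, near-complete capture gives a ratio close to 1, and a true benefit could outweigh the tilt. A ratio of 1.5 requires the sources common to both arms to miss half of all events; in the model above it arises only without the notes check. The change is worth making because safety is a stated goal and the cost is low.

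**What to change.** In the adverse event section {22}, add a field to the per-AE record for the source that first identified the event: checklist, notes entry not originating from the trial therapist, notes entry originating from the trial therapist, or trial therapist directly. Let the field also mark any other source that picked the event up. This matters because an event first heard in therapy and later found by the checklist must stay in the common-source count. If such events were dropped and the therapist always came first, the first row of the table would give (1 − 0.5) × 0.65 = 0.325 in TF-CBTp against 0.65 in TAU, a ratio of 0.50 in the opposite direction.

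In the auditing section {23}, for DMEC closed reports, and for the published results:

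- Base the between-arm comparison on events identified by the checklist or by notes entries not originating from the trial therapist, over the same follow-up period in both arms. Show the checklist alone as well, since therapist liaison might also make care teams more watchful.
- Show all-source counts alongside.
- List therapist-originated events separately, and use the existing cause code to separate therapy-specific events.
- Keep every event, whatever its source, for individual safety action.

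The cost is one extra field and one extra table. The common-source count will be smaller and less precise than the all-source count, which is why both should be shown.

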## Methods: participants, interventions, and outcomes

### Study setting {9}

There will be five recruiting sites across England (South London and Maudsley (SLaM); Greater Manchester Mental Health; Cumbria, Northumberland, Tyne and Wear; Oxford Health; Sussex Partnership), all of which are foundation NHS mental health trusts and have close links with Higher Education Institutions (HEIs) (King’s College London (KCL); University of Manchester; Newcastle University; Oxford University; University of Sussex). All secondary and tertiary care services within these trusts are potential sources of recruitment. Neighbouring trusts will be approached to act as Participant Identification Centres (PIC) for the recruiting sites if required.

The five NHS Trusts serve an ethnically diverse population and provide mental health care across a range of services in a variety of settings, ranging from adult Community Mental Health Teams, including Early Intervention for Psychosis services; inpatient wards and residential services; outpatient clinics and allied third sector services. Therapy will be delivered in community settings.

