AEs are defined by the Health Research Authority as any untoward medical occurrence, unintended disease or injury, or untoward clinical signs in participants, whether or not related to the treatment, which require additional support or input from health professionals. In addition, since an important subsidiary goal of the trial is to establish the safety of the intervention, issues specific to psychological therapies [103, 104], and specific concerns clinicians have about trauma-focused therapy with psychosis individuals, will also be monitored, namely clinically significant increases in mental health problems and/or risky or problematic behaviours; harm to self/others, including suicide attempts; harm from others; emergency room visits; or crises. Clinically significant increases will be operationalised as an unresolved exacerbation requiring increased involvement from the care team, e.g. requiring a change in treatment plan. Distress or complaints associated with therapy, completion of assessment measures, or any other trial procedure would also constitute AEs.

The causes for the AEs will also be recorded and monitored. For each AE, the following potential reasons will be identified: victimisation (aggressive behaviour, sexual abuse/assault, physical abuse/assault, emotional abuse/psychological maltreatment, exploitation, and other victimisation); mental health/psychological problems (excessive use of substances, general distress, psychotic symptoms, PTSD symptoms, suicidal ideation, and other psychological); trial procedures (group allocation, assessments, or therapy); physical health, including COVID-19; accidents or natural disasters; and other.

AEs will be assessed initially at three levels of severity, namely mild, moderate, and severe, which reflect the severity or impact of the event on the person at the time, and is distinct from seriousness. Seriousness relates to the outcome of the event and is the criteria for defining regulatory reporting obligations: SAEs are defined as death and life-threatening events (Category A), incidents which acutely jeopardise the health or psychological well-being of the individual, resulting in immediate hospital admission and/or persistent or significant disability or incapacity (category B), or resulting in injury requiring immediate medical attention (category C). However, in this study, any AE rated as ‘severe’ will automatically be classified as an SAE.

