AEs will be categorised for severity and seriousness by the site leads/Trial Coordinators. Relatedness to the trial will be judged based on whether the event resulted from administration of any of the research or therapy procedures, according to a temporal relationship (i.e. SREs). Unexpectedness of an event to the intervention will be judged based on whether the event is unexpected or unexplained given the participant’s clinical course, previous conditions and history, and concomitant treatments (i.e. USREs).

Events identified as SAEs will be further reviewed by the PI initially and additionally by the chair of the DMEC. Only SAEs that have been judged by the PI and the chair of the DMEC to be USREs will be reported to the REC. The DMEC will be responsible for investigating further, if there are any concerns about unexpectedly high rates of SAEs, SREs, or USREs, which may include being unblinded as to trial condition or seeking further data on adverse events, and will advise the TSC on any ethical or safety reasons why the trial should be prematurely ended. The Funder will immediately be notified on receipt of any information that raises material concerns about safety or efficacy, and of any recommendations from the DMEC to end the trial.

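### A hospital admission that is not immediate, or a prolonged stay, is not an SAE unless the event qualifies by another route, so it can miss SAE-level review

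*Protocol article*

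**What the plan says.** All of the following is from the protocol article.

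- **Seriousness, Adverse event reporting and harms {22}.** There are three categories. The first: "SAEs are defined as death and life-threatening events (Category A"). The second opens with "incidents which acutely jeopardise the health or psychological well-being of the individual". Hospital admission then enters it as one of the results that the incident must have: "resulting in immediate hospital admission and/or persistent or significant disability or incapacity (category B"). The third, category C, is injury needing immediate medical attention. The section says that seriousness concerns the outcome of an event.
- **Severity, same section.** AEs are graded mild, moderate or severe, grades "which reflect the severity or impact of the event on the person at the time, and is distinct from seriousness". Any AE graded severe "will automatically be classified as an SAE".
- **Governing guidance, same section.** Good Clinical Practice guidance for non-CTIMP studies "will be followed to make decisions regarding seriousness (i.e. AEs vs SAEs"). Its content is not reproduced.
- **Review route, same section.** Site leads or Trial Coordinators classify both severity and seriousness. Then: "Events identified as SAEs will be further reviewed by the PI initially and additionally by the chair of the DMEC". Only SAEs can go on to be judged unexpected and related, and so be reported to the ethics committee.
- **DMEC remit {21a}.** The incidence of SAEs is a listed monitoring item.
- **Study setting {9}.** All secondary and tertiary services are possible recruitment sources, and the trusts' settings include "inpatient wards and residential services". Therapy is delivered in the community.
- **Exclusion criteria {10}.** A current acute mental health crisis excludes; being an inpatient does not.

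**The concern.** The harm that clinicians fear from memory reprocessing is a worsening of psychosis (Background {6a}), and psychiatric admission is one of its more objective markers. The harms section itself describes significant worsening as an unresolved exacerbation that draws in more care-team input. That is a graded course, in which an admission may come some time after the initial event. A definition that turns on the admission being immediate fits that course poorly. One that omits longer stays does not register a worsening in someone who is already in hospital.

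At stake are the individual review of such events by the PI and the DMEC chair, their eligibility for ethics-committee reporting, and the completeness of the SAE count by arm. Sections {11b} and {22} both make establishing the safety of the intervention an important subsidiary goal.

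**Working it through.** The plan gives no figure to reproduce, so the check is to run cases through the definition as written.

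**Step 1. Classify the cases.** In cases 1 to 3 the event is not life-threatening, leaves no lasting disability and is not an injury needing immediate attention.

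| Case | Category A | Category B | Category C | Severe rule | Result |
|---|---|---|---|---|---|
| 1. Acute incident, immediate admission, rated moderate | no | yes | no | no | SAE |
| 2. Same, but admitted after a delay, rated mild or moderate | no | no | no | no | AE only |
| 3. Existing stay prolonged, rated mild or moderate | no | no | no | no | AE only |
| 4. Case 2 or 3, but rated severe | no | no | no | yes | SAE |
| 5. Case 2 or 3, but life-threatening, lastingly disabling, or an injury needing immediate attention | one of A, B or C applies | | | not needed | SAE |

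The gap is cases 2 and 3 only.

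**Step 2. Compare cases 1 and 2.** Both end in admission and differ only in timing. The section says seriousness concerns outcome, yet the two are classified differently. The article does not say how soon an admission must follow to be immediate, so sites could draw the line in different places.

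**Step 3. Does the severe rule close the gap?** Not by its terms. Severity is impact at the time of the event and is declared separate from seriousness. Nothing links an admission or a longer stay to a severe grade. An exacerbation graded moderate when recorded and followed by admission a week later can stay an ordinary AE.

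**Step 4. What is lost in cases 2 and 3?** The PI and DMEC-chair review, possible onward reporting as an unexpected serious related event, and inclusion in the SAE rates that the DMEC watches. The section prescribes none of these for a non-serious AE.

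**Step 5. Scale.** The documents give neither an admission rate nor a split by timing. Purely as an illustration, let *a* be the proportion of participants admitted over 24 months and *b* the share of those whose admission is not immediate or whose event prolongs a stay. The affected pool per arm is 150 × *a* × *b*:

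- assumed *a* = 0.20, *b* = 1/3: 150 × 0.20 × 1/3 = 10
- low, *a* = 0.10, *b* = 0.20: 150 × 0.10 × 0.20 = 3
- high, *a* = 0.30, *b* = 0.50: 150 × 0.30 × 0.50 = 22.5

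Both rates are assumptions. The result is the pool before removing events that qualify under case 4 or 5, so it is not an estimate of missed SAEs.

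**The case against.** A reader might infer that an admission is serious only when immediate, and that a prolonged stay is never serious. The text does not support that. The sentence after the category list makes every severe AE an SAE, and the life-threatening, disability and injury routes apply whatever the timing of admission.

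A reader might also infer that these harms go undetected. They do not:

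- A structured checklist is completed at each assessment and unblinded staff check clinical notes {22}.
- Exacerbations, crises and emergency visits are monitored as AEs {22}.
- The Trial Management Group receives monthly site reports on adverse events {5d}.
- Safety concerns identified through AEs can lead to therapy amendments or termination {11b}.
- The DMEC may ask for further AE data when it has concerns about SAE rates {22}.
- Service use is collected over the full 24 months.

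Nor do the documents support a claim of bias between arms, because the definition applies equally to both. The inpatient point is also limited: acute crisis is excluded and therapy takes place in the community. A participant admitted during follow-up could still have a stay prolonged.

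The strongest objection is that seriousness decisions are placed under Good Clinical Practice guidance, and that a journal article condenses a fuller protocol. The guidance may be broader, but it is not shown. What the article does state is an explicit definition. If the guidance is wider, classifiers at five sites have two standards to choose between; if it is not, the gap stands. Either way the two need reconciling.

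What stands of the objection is that the gap is confined to cases 2 and 3, and that what can be lost is SAE-level review and counting, not detection.

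**Conclusion.** The concern holds in this limited form. Under the stated definition, a non-immediate admission or an extended stay that is rated mild or moderate and meets no other criterion is an AE only, and it misses the oversight tied to SAE status. The severity rule narrows the gap without closing it, because the section keeps severity and seriousness apart.

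The conclusion rests on reading the article's wording as operative, and on the cited guidance not being applied in its place. The size is unknown; the illustrative pool depends entirely on assumed rates. The point is worth correcting because the change is small and makes the serious-event count by arm more complete on a harm that the trial set out to examine.

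**What to change.** 1. Reword the admission part of category B along these lines: *hospital admission, whether or not immediate, or prolongation of an existing admission*. Keep the disability limb as it is. When doing so, confirm that the category's opening condition about acute jeopardy is not read as bringing the timing requirement back.
2. Reconcile the category list with the Good Clinical Practice guidance cited in the same section, so that sites work from one standard.
3. Re-check AEs already recorded in both arms against the revised wording. The notes review and service-use data make this feasible.

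The cost is a one-sentence amendment to the definition and its procedure, a single pass through existing AE records, and a modest rise in SAEs for the PI and DMEC chair to review. The change affects classification and reporting only, not participants' care.
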